## Abstract

**Background:**

Vitamin D deficiency is common among otherwise healthy pregnant women and may have consequences for them as well as the early development and long-term health of their children. However, the importance of maternal vitamin D status on offspring health later in life has not been widely studied. The present study includes an in-depth examination of the influence of exposure to vitamin D early in life for development of fractures of the wrist, arm and clavicle; obesity, and type 1 diabetes (T1D) during child- and adulthood.

**Methods/design:**

The study is based on the fact that in 1961 fortifying margarine with vitamin D became mandatory in Denmark and in 1972 low fat milk fortification was allowed. Apart from determining the influences of exposure prior to conception and during prenatal life, we will examine the importance of vitamin D exposure during specific seasons and trimesters, by comparing disease incidence among individuals born before and after fortification. The Danish National databases assure that there are a sufficient number of individuals to verify any vitamin D effects during different gestation phases. Additionally, a validated method will be used to determine neonatal vitamin D status using stored dried blood spots (DBS) from individuals who developed the aforementioned disease entities as adults and their time and gender-matched controls.

**Discussion:**

The results of the study will contribute to our current understanding of the significance of supplementation with vitamin D. More specifically, they will enable new research in related fields, including interventional research designed to assess supplementation needs for different subgroups of pregnant women. Also, other health outcomes can subsequently be studied to generate multiple health research opportunities involving vitamin D. Finally, the results of the study will justify the debate of Danish health authorities whether to resume vitamin D supplementation policies.

## Background

More and more attention is now being paid to the importance of prenatal nutrition and the long-term influence of the mother’s nutrition for long-term health of the progeny, including the mother’s nutritional status prior to conception. The importance of this approach is supported by the newly released draft report from the Scientific Advisory Committee on Nutrition, commissioned by the British Health Department and the Food Standards Agency in 2010 [1]. The report highlights the need for a better understanding of the influence of nutritional exposure during critical time periods in human development and the type of dietary interventions that might be employed to improve child nutrition and elicit long-term health benefits. The present study addresses these issues in relation to vitamin D.

### Vitamin D

Vitamin D is a fat-soluble vitamin that is necessary for the human body. It plays an important role in a wide variety of chronic health conditions. The discovery of high-affinity vitamin D receptors (VDR) in many organs and cell types has led to an increasing focus on the role of vitamin D as a steroid hormone with significant influences on cell metabolism and proliferation. Widely distributed in body tissues, a VDR, once bound to a vitamin D ligand, travels to the nucleus where it binds to sites within the human genome and consequently influences the activity, or expression, of individual genes. A recent study reported identification of as many as 2,776 sites of vitamin D receptor binding and 229 genes whose expression was directly linked to changes in vitamin D levels [2]. Many of these genes are involved in bone and muscle development, metabolism and immune function. Consequently, low vitamin D influences bone health, body growth and composition, and also impacts on immunity [3,4]. Furthermore, as proposed in 2001, a critical window may exist during which vitamin D levels have a persisting impact on health outcomes [5]. Low vitamin D during gestation and in early life may therefore play an important role for susceptibility to bone fragility, obesity and autoimmune diseases later in life [6].

Vitamin D is synthesized in the skin when exposed to ultraviolet-B radiation from the sun. 7-dehydro-cholesterol is converted to cholecalciferol (vitamin D3) which is then, in kidneys, modified further to form the active vitamin binding to VDR. Animal tissues consumed as food provide additional sources of this hormone-like vitamin, while plant foods may provide the less potent form of vitamin D: ergocalciferol (vitamin D2) [7]. Although adequate exposure to UVB sunlight is paramount to an ample supply of vitamin D, oral intake, augmented by both fortification and supplementation, is necessary to maintain baseline stores in populations at high latitudes were the sun can only drive dermal synthesis of vitamin D from April to October [8]. It has been shown that fortification is particularly relevant for those with low stores, e.g. pregnant women [9].

### Importance of fetal vitamin D on health later in life

Vitamin D insufficiency is highly prevalent in both developed and developing societies. It is estimated that one in seven, or about 860 million people around the world, have vitamin D deficiency or insufficiency [9]. With the high general prevalence of vitamin D deficiency, the status of pregnant and lactating women is of particular concern. Low levels may have consequences for not only the mother but also for the early development and long-term health of her offspring, since fetal stores of vitamin D depend on maternal concentrations [10]. Pregnancy is a time of particular susceptibility to vitamin D deficiency, as both maternal and fetal demands for the vitamin need to be met [11,12]. The development of tissues and organs at different stages of fetal growth makes timing of deficiency during gestation of particular importance, as the interaction between differential development and deficiency can determine the effect on the child. For instance, mothers with babies born between February and April will have had low sun-related UVB exposure, and hence, lower vitamin D exposure for their offspring during the third trimester, while babies born between May and July will have had low exposure in their second trimester and those born between August and October will have had low exposure during the first trimester. Adverse health effects of low vitamin D may therefore be most evident in organs or tissues whose development occurs in these trimesters, e.g. obesity may be particularly associated with low vitamin D during the third trimester when adipose tissue is formed; fractures may be particularly associated with low vitamin D during the third and/or second trimester [13]; and T1D with low vitamin D during the first trimester.

To date, the relationship between vitamin D status during fetal life and long-term health has not been widely examined, and interventions are generally lacking. A few studies suggest that low fetal vitamin D may reduce bone mineral content, consequently leading to fragility fractures [14]. Possibly it also affects metabolic functioning and consequently leads to obesity [15]. Some studies have found that adult obesity varies as a function of month of birth and that subjects born from winter to spring become more obese, possibly due to low vitamin D levels from restricted maternal sun exposure during the third trimester of pregnancy [16]. Furthermore, a recent study reported that a low level of maternal vitamin D during pregnancy was related to high fat and low muscle in offspring at ages 5–9 [15]. Although mechanisms relating low perinatal vitamin D to later obesity are not well known, proposed mediators include epigenetic changes leading to initiation of adipogenesis, or induction of permanent functional changes in hypothalamic appetite regulation [17,18]. Furthermore, there are studies showing that low fetal vitamin D may lead to persistent changes in the immune system, thus possibly influencing the risk of developing autoimmune diseases such as T1D [14,19,20].

Most evidence linking prenatal nutrition to later disease comes from animal studies, or from natural experiments, such as the Dutch Famine during World War II or the Great Chinese Famine during the Great Leap Forward. Both studies suggest that prenatal malnutrition strongly impacts adult health, although neither indicates specific effects from the lack of vitamin D. The effect of vitamin D levels during gestation, thus, has never previously been followed in large populations. Furthermore, large-scale interventional studies are needed to examine how vitamin D exposure during pregnancy affects long-term health outcomes of offspring. Such studies may never be conducted due to the associated high financial and logistical costs. To study the influence of seasonal variation and timing of fetal exposure in relation to later effects of vitamin D on health outcomes, one requires even larger numbers of subjects to be followed over long time.

### Objectives and hypothesis

The present study relies on a unique societal experiment in which all margarine and low fat milk products consumed by the Danish population were fortified with vitamin D, during two distinct time periods: in 1961–1985 fortifying margarine with vitamin D was mandatory in Denmark and in 1972–1976 low fat milk fortification was allowed. The present study also relies on the fact that in Danish national administrative and large research databases data can be linked at the individual level. This allows for the examination of the effects of exposure to additional vitamin D via fortified foods during fetal life in relation to later development of particular diseases. Initially the present study will include an in-depth examination of the influence of exposure to vitamin D during pregnancy for development of fractures of the wrist, forearm, upper arm and shoulder, as well as fractures of ankle; development of obesity; and development of T1D during child- and adulthood. Furthermore, the large number of subjects that will be followed will ensure that the effects of vitamin D exposure in relation to the timing of the seasons of gestational development also can be examined. Additionally, a validated method will be used to determine neonatal vitamin D status using stored dried blood spots (DBS) from individuals who develop the aforementioned disease entities as adults and their time and gender-matched controls. The main hypothesis is that low levels of vitamin D during critical phases of development have adverse effects on the long term risk of developing the above mentioned disease outcomes, and that exposure to extra vitamin D from food fortification has beneficial effects preventing the mentioned diseases.

## Methods/design

### Study populations

In Denmark, from 1961 to 1985 vitamin D fortification of margarine was mandatory (1.25ὕμg/100ὕg), and from 1972 to 1976 fortification of low fat milk (2.5-3.8ὕμg/100ὕgὕmilk) was permitted. The vitamin D fortification of low fat milk was not mandatory and therefore not all low fat milk distributed in Denmark in the time period was fortified with vitamin D. Unfortunately, there are no national statistics indicating the proportion of milk consumed that was fortified with vitamin D. Nevertheless, the two well-defined time periods of vitamin D fortification provide a natural framework for comparing the effects of early exposure to vitamin D on the development of diseases later in life amongst exposed and non-exposed adjacent birth cohorts (Figure 1).

**Figure 1 F1:**
[figure not shown]
**Study cohorts. **The figure provides examples of designs for examining the effects of vitamin D fortification on development of diseases for a follow-up period of up to 50ὕyears. The birth (grey boxes with allowance for short “wash-out period” in between) and follow-up years (arrows) of individuals from subgroups exposed before and after birth are given in relation to initiation or termination of vitamin D fortification.

The study relies upon the well-defined adjacent time windows, as well as the complete registration of every citizen in Denmark via the Danish Civil registration System. Every citizen in Denmark alive April 1^st^ 1968 is assigned a civil registration (CPR) number, and this number can be used to link information, on an individual level, in the Danish birth, patient and medical registries; social and ethnic registries; and clinical and other large databases. Consequently, the study will include approx. 3 mio. individuals from nationwide birth cohorts between the 1930ies and today.

### Databases

In a first effort, we will examine influence of additional early exposure to vitamin D on subsequent development of fractures, obesity, and T1D.

#### Fractures

Using the CPR numbers, individuals will be individually linked to the Danish National Patient Registry for incident and recurrent diseases. The register contains information about hospital contacts, including diagnosis codes and procedure codes for all treatment received at Danish hospitals [21]; after 1994, outpatient treatment is also captured by the register. From 1977–1993, diagnoses were classified according to the WHO International Classification of Diseases (ICD-8) and from 1994 onwards according to ICD-10. The main study outcomes are fractures at wrist and hand level (ICD-8: 814–817; ICD-10: S62); fractures of forearm (ICD-8: 813; ICD-10: S52); fractures of shoulder and upper arm (ICD-8: 810–812; ICD-10: S42); and fracture of ankle (ICD-8: 824; ICD-10: S82.5, S82.6. S82.8).

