#### Perinatal exposure

Development of the disease outcomes will be compared for children born around the time when mandatory vitamin D fortification was initiated and terminated. The hypothesis is that individuals born 1–2 years after commencement of mandatory fortification (1961) and thus exposed to extra vitamin D during fetal development and for the next 24–25 years until 1985 (where fortification was ended), although unexposed thereafter, will have a lower lifetime risk of developing the aforementioned disease entities compared to individuals born 1 –2 years before fortification. Although also exposed to fortification for 24 – 25 years and unexposed thereafter, the latter group was unexposed during fetal life. Likewise, individuals born 1–2 years after mandatory fortification terminated in 1985, and who were unexposed to vitamin D both during fetal development and subsequently, will have a higher risk of later developing the diseases compared to those exposed during fetal life. Similar comparisons of disease development can be made in relation to higher exposure to vitamin D from 1972–1976, when fortified low fat milk was permitted.

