### Statistical analyses

For the time trend analyses (i.e. to compare time to debut of a disease) of fractures and T1D, cohort analyses with all individuals born in the respective years entering the cohorts at time of birth, and the key covariates being the year/month of birth, will be conducted using Cox regression models. For the time trend analyses of obesity, similar cohort analyses will be conducted, where linear regression models will be used for the BMI as a continuous trait and logistic regression models will be used for the categorical variables (i.e. overweight and obesity), again with the year/month of birth as the key covariate. Secular trends within multiple birth cohorts used before and after change in fortification will be addressed using appropriate adjustments. Gender differences will also be considered.

Case–control analyses are envisaged for a comparison of blood spot vitamin D levels between subjects with a disease outcome and subjects who have not developed this outcome. These analyses still are based on a cohort - the entire population who has a blood spot card available, but the sampling design will be a case-cohort design, where information about the exposure will be collected only for cases developed after entry in the cohort and matched controls, randomly selected within specified strata. These data can be analysed using the Cox regression models for the event-type outcome and the logistic regression models for the dichotomous outcomes. The adjustment for possible confounders will be of particular importance in these analyses.

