## Discussion

### Strengths and limitations

The study takes advantage of a vitamin D fortification policy implemented in Denmark almost fifty years ago, and nests this “societal experiment” in a setting where the effect of conditions from conception (and before) for development of certain diseases can be followed among individuals from birth through adulthood. The study is also possible due to complete registration of every citizen in Denmark via a civil registration number. This number can be linked, on an individual level, to the Danish birth, patient and medical registries; social and ethnic registries; and clinical and other large databases. The comprehensive linkage of different datasets makes it possible to study the mediation, confounding or modification of effects of vitamin D for selected conditions through the development of sophisticated models in which individuals can be followed for periods of up to 50 years. Moreover, the large number of subjects that will be followed ensures that the effects of vitamin D exposure in relation to the timing of the seasons and gestational development can also be examined. Nevertheless, the proposed study design implies several uncertainties, including so-called ecological fallacies, addressed below.

Fortification supplied 15% of vitamin D intake on average, which may be considered low, particularly when the sun exposure is not ample. However, vitamin D fortification is especially beneficial when vitamin D status is low [9], e.g. when the previous 6 months of UVB radiation from sun exposure in Denmark was too weak to induce vitamin D conversion in the skin [30]. The use of 50,000-100,000 individuals from adjacent birth years in the general population studies of events like fractures and diagnosis of T1D, a pivotal strength of this study, makes it possible to detect even minor effects of vitamin D.

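### For fractures, register data from 1977 limit the 1961 contrast to adult ages and the 1985 contrast to about the mid-20s, so the lifetime, childhood and from-birth claims exceed what each can show

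*Protocol article*

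**What the plan says.** All references are to the protocol article.

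- **Fractures.** The outcome comes from the national patient register, whose diagnosis coding is given as: "From 1977–1993, diagnoses were classified according to the WHO International Classification of Diseases (ICD-8) and from 1994 onwards according to ICD-10". The same section adds that "after 1994, outpatient treatment is also captured by the register".
- **Perinatal exposure.** For the 1961 start, "individuals born 1–2 years after commencement of mandatory fortification (1961") are "compared to individuals born 1 –2 years before fortification", and the hypothesis is worded as a lower lifetime risk. The 1985 stop follows with the opposite direction: "Likewise, individuals born 1–2 years after mandatory fortification terminated in 1985" are expected to have the higher risk. Similar comparisons are foreseen around the 1972–1976 milk fortification.
- **Statistical analyses.** Fractures are analysed in cohorts that everyone enters at birth, with "the key covariates being the year/month of birth, will be conducted using Cox regression models".
- **Claims about age.** The Abstract promises results on "development of fractures of the wrist, arm and clavicle; obesity, and type 1 diabetes (T1D) during child- and adulthood". Strengths and limitations says that effects "can be followed among individuals from birth through adulthood", with follow-up of up to 50 years. No end date is given.

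The text does not state at which ages fractures can be observed for each contrast, or that these ages differ.

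**The concern.** A Cox hazard ratio for birth cohort is an average over the ages at which both groups are under observation. People born around 1961 were already in their mid to late teens when register diagnoses begin. People born around 1985 had reached only their mid-20s when the article was written. The two margarine contrasts therefore describe fractures at largely different ages, while the text speaks of lifetime risk, of childhood and adulthood, and of follow-up from birth.

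Two conclusions are at stake. A null 1961 result could be taken as evidence against an effect on childhood fractures, which that contrast does not observe. And if the effect depends on age, the two switches could differ, or agree, because of the data window alone.

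**Working it through.** The plan gives no figure for the observable ages, so there is none to reproduce.

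**Inputs**
- Start of fracture observation: 1977, the earliest coding year in Fractures, read here as the start of usable diagnoses.
- Births 1–2 years either side of 1961: 1959–60 and 1962–63 (Perinatal exposure).
- Births 1–2 years after the 1985 stop: 1986–87. The exposed comparison years are not stated; 1983–84 is assumed by symmetry. The same rule is applied to the milk switches.
- End of follow-up: assumed 2011 (1961 + 50 years), range 2010–2013.

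**Formulas**
- Age at first observation = 1977 − birth year (0 if born in 1977 or later).
- Age at last observation = end year − birth year.
- Strict window: ages at which all birth years of both groups are observed.
- Wide window: ages at which at least one birth year in each group is observed.

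**Strict windows, end 2011**

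| Switch | Births compared | First joint age | Last joint age |
|---|---|---|---|
| Margarine start 1961 | 1959–60 v 1962–63 | 1977 − 1959 = 18 | 2011 − 1963 = 48 |
| Margarine stop 1985 | 1983–84 v 1986–87 | 0 | 2011 − 1987 = 24 |
| Milk start 1972 | 1970–71 v 1973–74 | 1977 − 1970 = 7 | 2011 − 1974 = 37 |
| Milk stop 1976 | 1974–75 v 1977–78 | 1977 − 1974 = 3 | 2011 − 1978 = 33 |

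The wide windows are 17 (1977 − 1960) to 49 (2011 − 1962) for the 1961 start, and 0 to 25 (2011 − 1986) for the 1985 stop. Single groups are seen over more ages: the 1962–63 births from age 14–15, and the 1983–84 births to age 27–28. Those extra ages have no comparison group.

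**Ages shared by the 1961 and 1985 contrasts**

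| End year | Strict | Wide |
|---|---|---|
| 2010 | 23 − 18 = 5 | 24 − 17 = 7 |
| 2011 | 24 − 18 = 6 | 25 − 17 = 8 |
| 2012 | 25 − 18 = 7 | 26 − 17 = 9 |
| 2013 | 26 − 18 = 8 | 27 − 17 = 10 |

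With the strict window and end 2011, the shared 6 years are 6/30 = 20% of the 1961 window and 6/24 = 25% of the 1985 window.

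**Calendar years of the shared ages.** The 1959–63 births pass through ages 18–24 in about 1977 (1959 + 18) to 1987–88 (1963 + 24, to the end of that year of age). That is under ICD-8 and before outpatient capture. The 1983–87 births do so in about 2001 (1983 + 18) to 2011 (1987 + 24), under ICD-10 with outpatients included.

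**Illustration with assumed inputs.** Suppose the true hazard ratio is 0.90 before age 18 and 1.00 after, and that 60–70% of fractures up to age 24 occur before 18. The 1961 contrast then has expected hazard ratio 1.00. The 1985 contrast has about exp(0.6 × ln 0.90) = 0.939 to exp(0.7 × ln 0.90) = 0.929. The documents support neither assumption, so this shows only the mechanism.

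**The case against.** A reader might infer that the plan uses one hazard ratio from each switch to confirm or refute the other, that this is its main safeguard against time trends, and that the small overlap makes such confirmation impossible. The documents do not support this reading.

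- No section sets a confirmation rule. Perinatal exposure states only that the effect should run the other way at the stop. The stated safeguards against confounding and trend are adjacent birth years, adjustment for secular trends and sibling pairs.
- If the hazard ratio is constant over age, as an unmodified Cox model assumes, the two estimates are comparable however few ages they share. If it is not, the shared ages still allow a direct comparison.
- The milk switches bridge part of the gap. The 1972 start covers about ages 7–37 and the 1976 stop begins at about age 3. However, milk fortification was voluntary, and the article says there are no national statistics on the share of milk fortified, so this is weaker evidence.
- The childhood-and-adulthood wording covers several outcomes, and across all switches both childhood and adult fractures are observed. That defends the wording for the study as a whole. It does not cover the lifetime hypothesis attached to the 1961 contrast, or entry at birth for its cohorts.
- The caption of Figure 1 says that the figure gives birth and follow-up years. The figure is not shown here, so it may disclose the windows. The claims in the text would still need to match it.
- An age interaction is ordinarily analysis-plan detail, and its absence from an article is no fault. The fault is that the article claims ages which its own dates exclude.
- Comparing only ages 18–24 would discard most of the data and compare fractures recorded differently in the two eras. This stands and limits what the fix should ask for.

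The planned robustness analysis on an adjusted age scale does not resolve the point: its stated purpose is to equalise duration of exposure. Starting the 1961 cohorts' time at risk in 1977 would correct the risk sets but would not supply fractures from before 1977.

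**Conclusion.** The point holds in a limited form. For fractures, the 1961 contrast is jointly observable from about age 17–18 to the late 40s, and the 1985 contrast from birth to about the mid-20s. They share about 6 years if follow-up ends in 2011, and 5–10 years across end dates 2010–2013 and both window definitions. The 1961 contrast therefore cannot test lifetime risk or childhood fractures, and follow-up from birth through adult life holds for neither margarine contrast.

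The start and the stop are directly comparable only over the shared ages, or under an assumed age-constant hazard ratio. Otherwise agreement or disagreement between their all-age estimates is ambiguous. That is weaker than saying that neither can inform the other, which does not follow.

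The result rests on 1977 being the start of usable fracture data, on the assumed 1983–84 comparison births, and on the assumed end date. The lower age limit of the 1961 contrast does not depend on the end date.

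**What to change.** 1. State the ages at which fractures are observable on both sides of each switch, with the end date of follow-up.
2. For fractures, limit the claims of lifetime risk, of childhood and adulthood, and of follow-up from birth to those ages. Say that the 1961 contrast does not test childhood fractures and that the 1985 contrast does not reach beyond about the mid-20s.
3. Report fortification hazard ratios in age bands common to all switches (for example under 18, 18–24, and 25 or older) beside the all-age estimate.
4. Judge consistency between the 1961 and 1985 switches mainly in the shared band. Note that the 1961 cohorts pass through it before outpatient capture and the 1985 cohorts after it. Use the milk switches as supporting evidence.

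The cost is some rewording and one interaction term, with no new data. The downside is wider intervals within bands than for the all-age estimate.
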